#### Measures of mediating variables

##### Parent-child interaction

To observe the interaction between parent and child, the **Family Interaction Task (FIT**) [35] is used. This observation measure consists of four tasks (guessing game, an enticing marble game (labyrinth), planning a birthday party and a difficult puzzle) and measures affective, behavioral and verbal interaction. The tasks are scored on three scales for the parent (positive responsiveness; quality of assistance; anger and hostility), three scales for the child (expressions of positive affect; persistence and diligence; anger, defiance and frustration) and three dyadic scales (collaboration and teamwork; dyadic negative affect; dyadic positive affect). Every scale ranges from 1 to 5; 1 represents a low score and 5 a high score on a specific dimension. Scores are assigned based on the whole session. Interrater reliability in previous studies ranged from .63 to .73 with children in their middle childhood in the United States [35] and from .87 to .94 with adolescents in the Netherlands [36].

To assess whether parent and child can construct a constructive narrative about emotions, a topic to which a lot of attention is paid in the intervention program, parent and child are asked to participate in the **Autobiographical Emotional Events Dialogue (AEED) **[37]. Within this task parent and child are asked to describe together four situations in which the child felt four different emotions (happy, sad, angry and scared). The narratives are scored on seven scales for the parent and seven parallel scales for the child (shift of focus; boundary dissolution; acceptance and tolerance; cooperation, involvement and reciprocity; hostility; resolution/closure of negative feelings; elaboration and structuring), and two overarching scales (adequacy of the story; coherence). Every scale ranges from 1 to 9 and the higher the score, the higher the level of the specific behavior. Parent and child can be classified as 1) emotionally matched, 2) emotionally unmatched: excessive, 3) emotionally unmatched: flat, and 4) emotionally unmatched: inconsistent. Interrater reliability in previous research ranged from .87 to .95 [38].

##### Treatment components in the children's sessions of the intervention program

##### Emotional security

The main goal of the children's sessions of the intervention program is for children to learn how to cope with their experiences and feel safe again. The **Security in the Family System scales (SIFS) **is a questionnaire especially developed to assess feelings of security within the family subsystem. To assess whether children feel safer after completing the program, they are administered the scale 'secure' of the SIFS. The internal consistency of this scale was .85 and the test-retest reliability was .82 in previous studies [39].

##### Coping strategies

In the children's sessions of the intervention program children are taught to seek support from significant others in times of need. Another part of the program is to play a game with the use of gross motor skills to release tension, after discussing possibly difficult subjects. Within the program children also learn to rephrase destructive thoughts such as feeling responsible for the occurrence of the interparental violence. Three of the five scales of the **How I Coped Under Pressure Scale (HICUPS) **[40] ask about these three strategies (seeking support, distraction and rephrasing thoughts). In another study the internal consistency of the Dutch translation of these scales was .77 for 'Distraction', .86 for 'Positive cognitive restructuring' and .88 for 'Seeking support' [41].

##### Feelings of guilt

Many children who experienced interparental violence feel guilty about what happened [42]. In the intervention program children are taught that the interparental violence was not their fault. To assess whether children internalize this message and feel less guilty after completing the program, they are administered the scale 'Self-blame' of the Dutch questionnaire **Cognitive Emotion Regulation Questionnaire (CERQ-k)**. Internal consistency of this scale was .79 in previous research [43].

##### Emotions

In every session children learn about different emotions, how to recognize these emotions and how to express them in a safe and constructive way. Children are asked to fill out the scale 'Differentiating Emotions' of the **Emotion Awareness Questionnaire (EAQ) **[44] to assess their ability to differentiate emotions. The internal consistency of this scale was .67 in a Dutch sample in a previous study [44]. To assess progress in the ability to express emotions, parents and children also participate in the observation task AEED [37] (for a detailed description see under 'parent-child interaction').

To assess possible effective elements of the intervention program all items of scales mentioned above, are combined in one questionnaire: 'Questionnaire for children about how to cope with difficult situations'. To assess whether children generalize learned coping strategies to different situations, they are asked to fill out the questions about coping strategies for two different situations: a situation in which they had an argument with one of their parents and a situation in which they had an argument with a friend, both in the past two weeks. To assess feelings of guilt in both situations the scale 'Self-blame' of the Cognitive Emotion Regulation Questionnaire is also administered for both situations.

#### Measures of moderating variables

##### Mental health of the parent

Posttraumatic stress symptoms of the parent are assessed with the Dutch version (translated by Olff, 2006) of the **Impact of Events Scale-Revised (IES-R) **[45]. This questionnaire consists of 22 items divided in three scales: intrusion, avoidance and hyperarousal. Parents rate their own behavior and thoughts of the past seven days on a 5-point Likert scale, ranging from 'not at all' (0) to 'very much'(4). Test-retest reliability (.76) and internal consistency (.94) were high in other research [46].

To assess anxiety and depression symptoms of the parent, the Dutch version of the **Hospital Anxiety and Depression Scale (HADS) **[47] is used. This screening instrument consists of seven items concerning depression and seven items concerning anxiety. Respondents are asked to answer on a 4 point scale and the total score of both subscales is interpreted. In other studies within the Netherlands internal consistency ranged from .82 to .90 for the 'Total score', from .80 to .84 for the subscale 'Anxiety', and from .71 to .86 for the subscale 'Depression'. The test-retest reliability (after three weeks) for the 'Total score' was .91, for the subscale 'Anxiety' was .89 and for the subscale 'Depression' was .86 [48].

##### Parenting stress

Parents who experience a lot of parenting stress may have less psychological resources left to benefit from the intervention. The overall parenting stress is measured with the short version of the **Parenting Stress Index (PSI) **[49], translated into Dutch [50]. The questionnaire consists of 25 items and covers child related stress as well as stress related to the parental role. The parent is asked to answer on a 6 point scale, ranging from 'totally disagree' (1) to 'totally agree' (6). The PSI can be used with parents of children aged 3-12 years. Internal consistency in previous studies ranged from .92 to .95 and validity seems acceptable [50].

##### Disturbances of attachment

To assess disturbances in the attachment relationship between parent and child after experiencing interparental violence, the parent is interviewed with the **Disturbances of Attachment Interview (DAI) **[51]. This interview is conducted by phone after T2. This semi-structured interview consists of twelve questions assessing symptoms of inhibited disturbances of attachment (5 items), disinhibited disturbances of attachment (3 items) and secure base distortions (4 items). A question is scored with 0 if the symptom is not present, 1 if the symptom is partly present, and 2 if the symptom is definitely present. Interrater reliability ranged from .71 (disinhibited) to .86 (inhibited) and internal consistency ranged from .67 (disinhibited) to .80 (inhibited) in a study with a sample of Dutch foster children [52]. Internal consistency of the secure base distortions taken together was .75 [53].

##### Duration and severity of the domestic violence

To determine what violent acts have occurred within the interparental relationship, parents are asked to fill out three scales ('Negotiation' (α = .86), Psychological aggression' (α = .79) and 'Physical assault' (α = .86)) of the **Revised Conflict Tactics Scales (CTS2) **[54]. A few questions about the duration of the interparental violence were added.

To assess whether children experienced other forms of child abuse or traumatic events, besides witnessing interparental violence, the **Conflict Tactics Scales Parent-Child (CTSPC) **(scales 'Overall physical assault towards the child' (α = .55), 'Psychological Aggression towards the child' (α = .60), 'Nonviolent discipline (α = .70), 'Neglect' (α = .22)) [55,56] and the **Parent Report of Traumatic Impact **[57] are administered to the parent.

To assess child abuse and neglect in the own childhood of the parent the **Adverse Childhood Experiences (ACE)-questionnaire **[58] is administered.

##### Demographic variables

A demographic questionnaire is used to collect participant's demographic information. This questionnaire consists of 14 questions concerning ethnicity, living situation, education, social economic status and age and gender of the child.

All questionnaires for parents and children are combined in an attractive booklet. All instruments will be administered at all three assessment moments, with the exception of the demographic variables (only at T1) and part of the questionnaire about duration and severity of domestic violence (CTS2 and ACE only at T1), the interview about disturbed attachment behavior (only at T2) and the observation tasks FIT and AEED (not at T1).

Figure 1 provides an overview of the instruments used at each assessment.

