## Abstract

**Background:**

Children who witness interparental violence are at a heightened risk for developing psychosocial, behavioral and cognitive problems, as well as posttraumatic stress symptoms. For these children the psycho-educational secondary prevention program 'En nu ik...!' ('It's my turn now!') has been developed. This program includes specific therapeutic factors focused on emotion awareness and expression, increasing feelings of emotional security, teaching specific coping strategies, developing a trauma narrative, improving parent-child interaction and psycho-education. The main study aim is to evaluate the effectiveness of the specific therapeutic factors in the program. A secondary objective is to study mediating and moderating factors.

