**Methods/design:**

This study is a prospective multicenter randomized controlled trial across cities in the Netherlands. Participants (N = 140) are referred to the secondary preventive intervention program by police, social work, women shelters and youth (mental health) care. Children, aged 6-12 years, and their parents, who experienced interparental violence are randomly assigned to either the intervention program or the control program. The control program is comparable on nonspecific factors by offering positive attention, positive expectations, recreation, distraction, warmth and empathy of the therapist, and social support among group participants, in ways that are similar to the intervention program. Primary outcome measures are posttraumatic stress symptoms and emotional and behavioral problems of the child. Mediators tested are the ability to differentiate and express emotions, emotional security, coping strategies, feelings of guilt and parent-child interaction. Mental health of the parent, parenting stress, disturbances in parent-child attachment, duration and severity of the domestic violence and demographics are examined for their moderating effect. Data are collected one week before the program starts (T1), and one week (T2) and six months (T3) after finishing the program. Both intention-to-treat and completer analyses will be done.

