In addition to the study of program effectiveness, evidence for mechanisms of change and predictors of effectiveness may further support the intervention design. Graham-Bermann and her colleagues (2011) pioneered the study of specific mediators and moderators, focusing on parenting and mental health of the mother as mediators and degree of exposure to family violence and demographic variables as moderators [10]. The current study will focus on parent-child interaction, emotional security and taught skills (coping strategies, feelings of guilt, the ability to differentiate and express emotions) as mediators and mental health of the parent, parenting stress, disturbances in parent-child attachment, duration and severity of the domestic violence and demographics as moderating variables.

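### The attachment-disturbance moderator is measured only after the program ends, so moderation by it cannot be separated from a treatment effect and cannot directly guide intake decisions

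*Protocol article*

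**What the plan says.** The role is stated twice. The Abstract (Methods/design) says that "disturbances in parent-child attachment, duration and severity of the domestic violence and demographics are examined for their moderating effect". The Background lists "disturbances in parent-child attachment, duration and severity of the domestic violence and demographics as moderating variables".

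The only instrument for this construct is the Disturbances of Attachment Interview, described under Measures of moderating variables, in Disturbances of attachment: "This interview is conducted by phone after T2". The schedule at the end of Demographic variables agrees, naming as an exception "the interview about disturbed attachment behavior (only at T2". T2 falls after the program: "Data are collected one week before the program starts (T1), and one week (T2) and six months (T3) after finishing the program".

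The general rule for the other instruments is "All instruments will be administered at all three assessment moments, with the exception of the demographic variables (only at T1", followed by the remaining exceptions. Parental mental health (IES-R, HADS), parenting stress (PSI), violence history and demographics therefore all have a T1 value, as the legend of Figure 1 confirms.

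On what the program does, the Abstract (Background) includes among its specific factors "developing a trauma narrative, improving parent-child interaction and psycho-education". The section on the intervention program names attachment theory as one of its two theoretical bases, and the first section on Parents' sessions sets greater parental sensitivity as a goal. The Discussion says that knowing for whom the program works should help refine screening at intake and selection for participation.

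**The concern.** A moderator analysis asks whether the program works differently in children who differed before it began. The variable has to be fixed before treatment, or at least be something treatment cannot change. Here it is recorded once, after nine child and nine parent sessions, in a trial whose active program targets a closely related construct. The article itself classes parent-child interaction, observed at T2 and T3, as a mediator, while attachment disturbance, measured after T2, is classed as a moderator.

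If the program changes the interview score, families with the same T2 score in the two arms are no longer comparable groups formed by randomisation. An arm-by-score interaction then mixes true moderation with the program's effect on the score. Two things are at stake: the validity of this one secondary result, and its use at intake, where only a pre-program score is available.

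**Working it through.** **1. The plan's own figure.** Sample size calculation gives power .80 for a regression with N = 90, f² = 0.15, alpha .05 and five predictors. With a noncentral F test, noncentrality 0.15 × 90 = 13.5 and df (5, 84), power is 0.793, so the figure reproduces. It does not depend on when a moderator is measured, so it neither supports nor answers the point.

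**2. Timing, side by side.**

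| Moderator | Value before the program? |
|---|---|
| IES-R, HADS, PSI | Yes (T1, T2, T3) |
| CTS2, ACE, demographics | Yes (T1 only) |
| Attachment disturbance | No (once, after T2) |

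No section supplies another attachment measure at T1, or an argument that the score is stable over nine sessions.

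**3. A two-stratum example (all inputs assumed).** Suppose 40% of children are disturbed at baseline, controls do not move, and the program moves a quarter of the disturbed out of that group. The disturbed stratum at T2 is then 0.40 × 0.75 = 30% of the intervention arm and 40% of controls. Give undisturbed children mean symptoms 0, disturbed children who would not move mean *a*, and those who would move mean *b*. Let the program lower symptoms by the same amount *d* in every child, so there is no true moderation.

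- Disturbed at T2: intervention *a* − *d*; control 0.75*a* + 0.25*b*. Difference: 0.25(*a* − *b*) − *d*.
- Undisturbed at T2: intervention (0.10/0.70)*b* − *d* = *b*/7 − *d*; control 0. Difference: *b*/7 − *d*.
- False interaction: 0.25(*a* − *b*) − *b*/7.

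With *a* = *b* = 0.8 SD it is −0.8/7 = −0.11 SD. With *a* = 1.0 and *b* = 0.4 it is 0.15 − 0.057 = +0.09 SD. It is zero when *b* = 0.25/(0.25 + 1/7) × *a* ≈ 0.64*a*. The sign is therefore not fixed.

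**4. Simulation (4,000 trials per row, N = 90, 2:1 allocation).** Assumed, not in the documents: T1–T2 correlation of the score 0.7; slope of outcome on the T1 score 0.4; average program effect −0.5; residual SD 0.8. The model is outcome on arm, score and arm × score. Shared response means that a child's individual response moves score and outcome together.

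| Scenario | Interaction, T1 score (rejected) | Interaction, T2 score (rejected) |
|---|---|---|
| No true moderation; program leaves score alone | 0.00 (5.0%) | −0.01 (5.3%) |
| No true moderation; uniform shift 0.5 SD | 0.00 (4.8%) | 0.00 (4.6%) |
| No true moderation; shift 0.3, shared response SD 0.3 | 0.00 (4.7%) | 0.06 (5.7%) |
| No true moderation; shift 0.5, shared response SD 0.5 | 0.00 (3.9%) | 0.14 (10.3%) |
| No true moderation; shift 0.5, shared response SD 0.7 | 0.00 (2.5%) | 0.24 (21.2%) |
| True interaction −0.40; program leaves score alone | −0.41 (58.7%) | −0.28 (32.5%) |
| True interaction −0.40; shift 0.5, shared response SD 0.5 | −0.40 (46.7%) | −0.08 (7.0%) |

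Two rows check by hand. With no program effect on the score, the true interaction is diluted to −0.40 × 0.7 = −0.28. With a uniform shift, the arm coefficient moves from −0.50 to −0.50 + 0.4 × 0.7 × 0.5 = −0.36, because part of the effect is conditioned away, although no false interaction appears.

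**The case against.** The best defence is that an effect of the program on attachment disturbance is plausible but not shown. Reducing such disturbance is not among the listed program goals, and parent-child interaction has its own measures, FIT and AEED. The control program also has nine parent sessions and reunites parent and child after each session, so the arms may differ less in attachment change than the example assumes. If the score is untouched, the T2 value is only a noisy stand-in for baseline, with error rates near nominal. This stands, and it limits the claim. It does not remove the point, because without a T1 score the trial cannot show which case applies. An arm comparison at T2 would be indirect evidence only.

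Three stronger readings are tempting and not supported:

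- A reader might infer that a false interaction must appear even if the program helps every child equally. The algebra and the simulation show that it can be zero or of either sign. Children who remain disturbed are non-responders on attachment, not necessarily on symptoms.
- A reader might call the result uninterpretable altogether. That holds only for moderation by a pre-treatment characteristic, which is what the intake aim needs.
- A reader might say that every family that leaves before T2 lacks the interview. Under Drop-outs, families who leave the program are still followed up, and the interview is by phone. Only families who cannot be reached necessarily lack it.

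The scope is also narrow: one moderator among several, under a secondary objective, and no passage ties intake criteria to this score alone.

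**Conclusion.** The point holds in a limited form. The timing, the moderator role and the absence of a T1 value are explicit, and no analysis plan can recover a baseline that was not collected. As designed, the trial cannot separate moderation by pre-program attachment disturbance from a program effect on the score, and the score cannot directly inform intake.

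The size of any bias cannot be determined from the documents. Under the assumptions shown it runs from about none to a false-positive rate of 21.2%, and a true interaction of −0.40 may be diluted to −0.28 or nearly lost at −0.08. These figures illustrate a range and are not estimates for this trial. The primary comparison and the moderators measured at T1 are not affected. The change should be made, but the trial's main conclusion does not depend on it.

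**What to change.** For families still to be enrolled, hold the interview before the program starts, at or before T1, and use only that score as a moderator. Ideally it precedes disclosure of the condition. Consent comes before randomisation and disclosure comes two weeks before the start (Blinding), so there is a window for the call. Disclosure is a preference, not a condition: the other T1 moderators are collected one week before the start, after disclosure.

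For families already past that point, do not use the T2 score as a moderator. Report it as a post-treatment outcome, as the arm difference at T2, and state the limitation.

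The cost is an existing phone call moved earlier and an amendment to the ethics committee, for which Ethical considerations gives the route. The sample for this moderator will be smaller, because data collection was already in progress (Status of the trial). The article does not say how many families remain to be enrolled, so the shortfall against the planned N = 90 is unknown. If too few remain, dropping the interview from the moderator list and reporting it as an outcome is still possible and needs no new data.

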#### Control variables

To make sure changes in the child's behavior are attributable to the intervention program, intervening life events that occur between the start of the program and during the follow up period, and treatment integrity are measured.

##### Intervening life events

To assess whether a change in the child's behavior is not attributable to stressful life events that occur between the start and finish of the program, in every session therapists keep score of new potential stressful or traumatic experiences in the life of the child. At T2 and T3, the post-test and follow-up assessments, parents fill out a checklist of life events in the last three (T2) or six (T3) months.

##### Treatment integrity

At least one, but preferably more parent and child sessions, of the intervention and control programs are randomly chosen and video-taped to be able to assess if the program is carried out according to the protocol. Ten percent of the video tapes will be randomly selected to be coded.

### Sample size calculation

The total sample size is based on the expected differences in outcome measures between children participating in the secondary prevention program 'En nu ik...!' and the control program 'Jij hoort erbij'. Because the effect of the intervention program has been tested before in a non-experimental design [22], a conservative estimate of f = 0,25 [59] is made about the effect size. Based on an alpha of .05, a power of .80 in a two tailed test, 48 subjects in each condition are needed.

To answer the research questions concerning the influence of potential mediators and moderators on the effectiveness of the secondary prevention program, several multiple regression analyses with different predictors will be performed. Based on an alpha of .05, an expected medium effect size of f^2 ^= 0.15 and a N = 90 we will be able to achieve a power of .80 for a model with up to five predictors. In smaller models of up to two predictors it will also be possible to draw conclusions about the independent contribution of each predictor.

Because of the tumultuous time these families are in we expect a relatively high drop-out rate of around 45% from T1 to T3. For this reason, we aim to recruit 250 children and parents.

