### Study population

140 children (6-12 years of age) and their caregiving custodial parents who experienced interparental violence will participate in this study.

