**Figure 1 F1:**
[figure not shown]
**Research procedure**. After informed consent is obtained, 2/3 of all parent-child dyads will be randomized into the experimental arm and 1/3 into the control arm. Parents and children are asked to fill out questionnaires (parent: TSCYC, CBCL, Questionnaire about duration and severity of domestic violence, demographic questionnaire, IES-R, HADS, PSI; child: CDI, TSCC, Questionnaire for children how to cope with difficult situations) at the first assessment (T1). A week later the program starts for all parents and children. One week (T2) and six months (T3) after the end of the program parents and children who take part in the study are again invited to fill out questionnaires and participate in two observation tasks (FIT and AEED). To check up on parents in the period between T2 and T3, parents are contacted by phone two times. At all assessments the teacher is also sent a questionnaire.

Parents receive €15,- after completing the first assessment, €25,- after participating in the program and completing the second assessment and €40,- after completing the follow up assessment. Children receive a gift after each assessment.

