### Data analyses

Most analyses will be done using the software program SPSS. Intention-to-treat and completer analyses will be performed. Descriptive analyses will be carried out by standard methods. The change in behavior will be assessed on a continuous scale, taking into consideration the scale of the different variables. For analyses of the primary outcome measures, we plan to use ANOVA repeated measure analyses and the scores of the children in the intervention group will be compared with their own scores on a previous assessment, as well as with scores of children in the control group at the same assessment. Mediator and moderator models will be tested, using data of all children (intervention and control group). Analyses and reporting of the results will be done according to the CONSORT 2010 Statement-guidelines [60].

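### The requirement of 48 per condition does not follow from its stated inputs in a simple comparison, contradicts the 2:1 allocation, and is not reconciled with the totals of 140 and 250

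*Protocol article*

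**What the plan says.** All references are to the protocol article.

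- **Sample size calculation, effect size:** "a conservative estimate of f = 0,25 [59] is made about the effect size".
- **Sample size calculation, requirement:** "Based on an alpha of .05, a power of .80 in a two tailed test, 48 subjects in each condition are needed". The section names no test for this figure and gives no correlation between assessments.
- **Sample size calculation, drop-out and recruitment:** "we expect a relatively high drop-out rate of around 45% from T1 to T3", followed by "For this reason, we aim to recruit 250 children and parents".
- **Figure 1 legend, allocation:** "2/3 of all parent-child dyads will be randomized into the experimental arm and 1/3 into the control arm".
- **Study population:** "140 children (6-12 years of age) and their caregiving custodial parents who experienced interparental violence will participate in this study". The Abstract (Methods/design) agrees: "Participants (N = 140) are referred to the secondary preventive intervention program". Neither place says whether 140 is counted before or after drop-out.
- **Data analyses, primary outcomes:** "we plan to use ANOVA repeated measure analyses". Both intention-to-treat and completer analyses are planned. The Drop-outs section carries the last value forward when questionnaires are not returned.

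**The concern.** The requirement is worded for two arms of equal size, while the design puts two thirds of the dyads in one arm. The effect size, alpha and power beside it do not lead to 48 per arm in the most direct reading, a two-group comparison at one assessment. Three totals are then in play (96 as 2 × 48, 140 and 250), and the article does not say how one leads to the next.

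The ethics committee, the funder and later readers rely on this section to judge what a null result means. The trial asks whether a trauma focus adds anything to nonspecific attention, so overstated power would let a null result count for more than it should. Data collection was in progress when the article was written, so it also matters which total is the recruitment target.

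**Working it through.** **Inputs.** f = 0.25, two-sided alpha .05, power .80, 48 per condition, about 45% drop-out and 250 recruited (Sample size calculation); 2:1 allocation (Figure 1 legend); 140 (Abstract, Study population). I take 250 as a count of parent-child dyads.

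**1. Effect size.** For two groups d = 2f = 0.50.

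**2. Reproducing 48.** With z-values 1.960 and 0.842, ((1.960 + 0.842)/0.50)² = 31.4.

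- Equal arms: 2 × 31.4 = 62.8, so 63 per arm, or 64 with the exact t. This does not give 48.
- 2:1: the control arm needs 1.5 × 31.4 = 47.1, so 48, with 96 in the intervention arm and 144 in all. Here 48 appears, but as the smaller arm only.
- Repeated measures, equal arms, between-group effect over m assessments with correlation r: λ = f² × N × m / (1 + (m − 1)r). At N = 96, m = 2, r = 0.5: λ = 0.0625 × 96 × 2 / 1.5 = 8.0, power 79.9%. At m = 3, r = 0.6: λ = 18 / 2.2 = 8.18, power 80.8%. At r = 0.8 power is 72% (m = 2) or 74% (m = 3). So 48 per arm is recovered at r of about 0.5 to 0.6, a value the article does not give.
- Analysis of covariance with an assumed baseline correlation of 0.5 also gives 48 per arm.

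**3. Power of a simple comparison** (noncentral t, noncentrality 0.50 × √(n₁n₂/(n₁ + n₂))):

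| Intervention v control | Noncentrality | Power |
|---|---|---|
| 48 v 48 | 2.449 | 67.9% |
| 64 v 64 | 2.828 | 80.1% |
| 96 v 48 | 2.828 | 80.2% |
| 93 v 47 (140 analysed, 2:1) | 2.794 | 79.2% |
| 92 v 46 (250 recruited, 45% lost) | 2.769 | 78.5% |
| 51 v 26 (140 enrolled, 45% lost) | 2.075 | 53.5% |

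**4. Reconciling the totals at 45% loss.**

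- 96 completers: 96 / 0.55 = 174.5, so 175 recruits.
- 144 completers: 144 / 0.55 = 261.8, so 262 recruits.
- 250 recruits: 250 × 0.55 = 137.5 completers, of whom one third, 45.8, are controls.
- 140 with no loss: 140 / 3 = 46.7 controls. After 45% loss: 140 × 0.55 = 77, of whom 25.7 are controls.

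The target of 250 follows from neither 96 nor 144, and neither 250 after loss nor 140 leaves 48 controls.

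**5. If the repeated-measures reading was meant.** Equal arms of 48 have n₁n₂/(n₁ + n₂) = 24. At 2:1 with c controls this quantity is 2c/3, so c = 36 and the requirement is 72 + 36 = 108. The wording therefore fails to describe a 2:1 design on this reading too.

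**The case against.** The strongest reply is that 68% belongs to a trial nobody planned: a single-occasion test with equal arms. Repeated-measures ANOVA is the stated analysis, and 48 per arm gives about 80% there with an ordinary correlation. If f is taken as a group-by-time effect in the usual power formula, power at N = 96 exceeds 98% for any r from 0.3 to 0.8. A condensed article may leave the test and the correlation to the full protocol. This stands as far as it goes: the missing correlation alone is not proof of error. It does not rescue the equal-arm wording, which conflicts with the article's own 2:1 ratio whichever test was used.

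The reply also holds that the planned trial is close to adequate. With 250 recruited, the control arm is about two children short of 48 and simple-test power is about 1.5 points below 80%, which is within the precision of a drop-out rate given as approximate. Intention-to-treat with last value carried forward would keep about 167 v 83, a nominal 96% if carrying values forward did not dilute the effect. All of that stands. The completer basis is used here because the section itself inflates for drop-out.

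Two stronger readings are tempting. A reader might infer that the trial as planned has only 68% or 54% power. The documents do not support this: 68% is for 48 v 48 in a simple test, and 54% requires 140 to be the enrolled number although 250 is the stated recruitment target. A reader might also infer that 48 is certainly the control arm of a 2:1 calculation and 140 certainly the T3 completers. Both are plausible, but 48 has other derivations, and 140 fits 96 × 1.45 = 139.2 as well as 250 × 0.55 = 137.5.

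**Conclusion.** The statement is wrong as written. For a simple two-group comparison its inputs give 68% power at 48 v 48 and require 64 v 64. For the stated 2:1 allocation they require 96 + 48 = 144. It can be defended at equal arms only with a correlation of about 0.5 to 0.6 that the article does not state, and equal arms are not the design. The figures 96, 140 and 250 are not reconciled.

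The practical size is modest if 250 is the true target: about 92 v 46 completers and about 78.5% power. It is large, about 54%, only if 140 is the number enrolled. These figures rest on d = 0.50, two-sided .05, a loss of 45% equal in both arms, 250 counted as dyads, and a simple completer comparison. None allows for the randomisation of whole groups, which would lower them.

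**What to change.** 1. In Sample size calculation, restate the requirement for the 2:1 design. For a simple comparison this is 96 + 48 = 144 analysable at T3. If repeated measures was the basis, name the test and effect, give the correlation and the number of assessments, and give the 2:1 arm sizes.
2. In the Abstract, Study population and Sample size calculation, state whether 140 and 250 are numbers recruited or numbers analysed, and whether 250 counts dyads. The investigators should supply the meaning of 140; it should not be guessed.
3. Report the power expected with 250 recruited at 2:1 and 45% loss: about 78.5% for a simple completer comparison, before any allowance for randomised groups.

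The cost is wording and a slightly less favourable power figure. No change in recruitment is needed.
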